# Randomized double-blind, placebo-controlled study of topical diclofenac in the prevention of hand-foot syndrome in patients receiving capecitabine (the D-TORCH study)

**DOI:** 10.1186/s13063-022-06353-2

**Published:** 2022-05-19

**Keywords:** Capecitabine, Hand-foot syndrome, Diclofenac, Celecoxib, Pyridoxine, Breast cancer, Gastrointestinal cancer, Prevention

## Abstract

**Introduction:**

Hand-foot syndrome (HFS) is a common cutaneous side effect of capecitabine therapy. Apart from oral cyclooxygenase-2 (COX-2) inhibitor (celecoxib), there are no proven strategies for the prevention of HFS. However, celecoxib is associated with significant cardiotoxicity. To date, no study has evaluated the role of topical COX inhibitor, diclofenac. In this study, we aim to compare topical 1% diclofenac gel with placebo in the prevention of capecitabine-induced HFS.

**Methods:**

This is a randomized, placebo-controlled, double-blind, parallel-group superiority trial: the Diclofenac Topical in Reducing Capecitabine induced HFS (D-TORCH) study. A total of 264 patients with breast and gastrointestinal malignancies will be randomly allocated (stratified by sex and type of therapy [monotherapy or combination regimen with capecitabine]) to receive either 1% topical diclofenac or placebo that will be applied over the palmar and dorsal surface of the hands twice daily whilst taking capecitabine for 12 weeks. The patients will be followed up until the end of four cycles. The primary objective of this study is to compare the effect of topical diclofenac with placebo in preventing HFS (incidence of NCI CTCAEv5.0 grade 2 or higher HFS). The secondary objective is to compare the effect of topical diclofenac with placebo on preventing all grades of HFS (incidence of NCI CTCv5.0 all grade HFS), time to develop HFS (from the start of capecitabine), patient-reported outcomes (PROs) (HF-HRQoL questionnaire), adherence with the application (self-reported), capecitabine dose changes (number of patients with dose modifications due to HFS) and safety profile (NCICTCv5.0 all grade HFS)

**Discussion:**

The D-TORCH study aims to determine if 1% topical diclofenac reduces the incidence of grade 2 or higher HFS in patients receiving capecitabine. To date, there have been a lot of trials for hand-foot syndrome prevention using agents like pyridoxine, vitamin E, carvedilol, and various polyherbal formulations, but none has been found successful. If the trial meets the primary end point, 1% topical diclofenac will be the new standard of care for HFS prevention.

**Trial registration:**

Clinical Trials Registry of India CTRI/2021/01/030592. Prospectively registered on January 19, 2021

## Administrative information

Note: The numbers in curly brackets in this protocol refer to SPIRIT checklist item numbers. The order of the items has been modified to group similar items (see http://www.equator-network.org/reporting-guidelines/spirit-2727-statement-defining-standard-protocol-items-for-clinical-trials/).

## Background and rationale {6a}

Capecitabine is an oral prodrug which is selectively transformed to its active moiety, 5 fluorouracil by the enzyme thymidine phosphorylase [1]. Capecitabine is commonly administered as a first and subsequent line agent in adjuvant/metastatic colorectal cancer and other gastrointestinal cancers, in patients with metastatic breast cancer who are resistant to taxane and anthracycline therapy, and pathological residual disease in patients with triple negative breast cancer following neoadjuvant chemotherapy [1–4]. Common dose-dependent toxicities of capecitabine include diarrhoea and hand-foot syndrome (HFS) [1].

HFS, also known as palmoplantar erythrodysesthesia, is characterized by painful erythema, edema of the hands and feet and varying degrees of dysesthesia, followed by skin desquamation [5]. The incidence of capecitabine-induced HFS is around 50 to 60%, whilst the severe forms account for 20–30% of cases [1]. HFS is usually self-limiting and rarely leads to severe life-threatening manifestations. In severe cases, however, it may necessitate dose interruptions, modifications, and permanent discontinuation of capecitabine [6, 7]. In addition, it may also impair the quality of life. Prior studies suggest that the peak occurrence of HFS is observed in the second cycle of capecitabine, whilst approximately 90% of HFS will be diagnosed by the fourth cycle of capecitabine [5, 8].

Several pathophysiological mechanisms of capecitabine-induced HFS have been hypothesized [9–11]. One such mechanism includes the upregulation of cyclooxygenase (COX)-2 expression [9]. Therefore, the use of COX-2 inhibitors may prevent capecitabine-induced HFS. In this respect, Lin et al. conducted a retrospective study to compare the incidence and severity of HFS in 67 patients with metastatic colorectal cancer who were subjected to capecitabine therapy with or without celecoxib and reported that the capecitabine/celecoxib group had a significantly lower rate of grade 1 HFS and a non-significant but marked reduction in grade 2 HFS as compared with the capecitabine-alone group [12]. Further, Zhang et al. performed a phase II randomized trial to assess the prophylactic efficacy of celecoxib on capecitabine-induced HFS in 110 stage II and III colorectal cancer patients and observed that celecoxib significantly reduced the incidence of grade 1 and grade 2 HFS [13]. The findings were confirmed in a phase III study by Zhang et al [14]. Despite its proven efficacy in preventing capecitabine-induced HFS, celecoxib is not widely used because of concerns for cardiotoxicity [15]. Karimi et al. reported that a polyherbal hydrogel containing *Calendula officinalis* results in fewer complications and symptoms associated with HFS in patients receiving fluoropyrimidine drugs [16]. Elif et al. reported that pyridoxine, vitamin E, emollient creams, and henna were likely to be effective in HFS symptom alleviation, but the exact doses and duration have not been ascertained [17]. Da Silva et al. noted that the release of norepinephrine from sympathetic skin terminals leads to the activation of beta 2 adrenergic receptors contributing to the upregulation of pro-inflammatory cytokines. This paves the way for use of topical agents like carvedilol, but the final results are awaited [18].

Topical non-steroidal anti-inflammatory drug inhibitors (NSAIDs), such as diclofenac, can inhibit COX-2 locally and may have a role in preventing HFS, without systemic side effects. However, no study to date has evaluated the role of topical COX inhibitors in the prevention of capecitabine-induced HFS. Therefore, this study aimed to evaluate the efficacy and safety of topical diclofenac in preventing capecitabine-induced HFS.

### Objectives {7}

We hypothesize that the application of 1% topical diclofenac will decrease the incidence of capecitabine-induced HFS (grade 2 or higher) by 15%, when compared with placebo.

The primary objective of this study is as follows:

1. To compare the effect of topical diclofenac with placebo in preventing HFS (incidence of NCI CTCAEv5.0 grade 2 or higher HFS)

The secondary objective is to compare the effect of topical diclofenac with placebo on the following:Preventing all grades of HFS (incidence of NCI CTCv5.0 all grade HFS)Time to develop HFS (from the start of capecitabine)Patient-reported outcomes (PROs) (HF-HRQoL Questionnaire)Adherence with the application (self-reported)Capecitabine dose changes (number of patients with dose modifications due to HFS)Safety profile (NCICTCv5.0 all grade HFS)

The tertiary correlate objectives are as follows:

1. To correlate the occurrence and severity of HFS with COX-2 levels (serum COX-2 levels)

2. To correlate the occurrence and severity of HFS with genetic polymorphism of dihydropyrimidine dehydrogenase (DPD) enzyme

The primary assessment time for the primary outcome is 4 cycles of capecitabine-based therapy, which amounts to 12 weeks.

### Trial design {8}

The Diclofenac Topical in Reducing Capecitabine induced HFS (D-TORCH) study is a single-centre, parallel-group, double-blind, 1:1 randomized placebo-controlled, superiority trial.

There was no public or patient involvement in the design of the protocol.

## Methods: participants, interventions, and outcomes

### Study setting {9}

The study will be conducted in the outpatient breast cancer and gastrointestinal cancer clinics at the [name] Institute Rotary Cancer Hospital (IRCH), New Delhi, India. The IRCH is the cancer block of the All India Institute of Medical Sciences, New Delhi, a central government-funded tertiary care hospital and academic centre. The IRCH caters to a large population (over 20 million) in Delhi, and neighbouring states, and registers over 15,000 patients with cancer annually.

### Eligibility criteria {10}

To be eligible to participate in the study, patients must meet all the following inclusion criteria:Age ≥ 18 yearsStarting capecitabine for breast and GI malignancies, either in adjuvant/neoadjuvant or palliative settingCommencing capecitabine at a dose of ≥ 1000 mg/m^2^ twice daily every 2 out of 3 weeks as single-agent chemotherapyLife expectancy greater than 12 weeksEastern Cooperative Oncology Group (ECOG) performance status 0–2Able to start study treatment within 14 days of randomizationWilling and able to comply with all study requirements, including treatment (applying diclofenac gel), timing, and/or nature of required assessmentsSigned, written informed consent

Patients meeting any of the following criteria will be excluded from the trial:Pre-existing grade 2 or higher neuropathy confounding assessment of HFSOther dermatologic conditions that in the opinion of the physician may affect the hands or feet or may complicate the evaluation during study treatmentConcurrent or planned use of pyridoxineAllergic or anaphylactic reactions with NSAIDsHistory of asthma, urticaria, or other allergic-type reactions after taking aspirin or other NSAIDsPatients receiving oral or topical NSAIDs for other conditionsConcurrent illnesses, including severe infections that may jeopardize the ability of the patient to undergo the procedures outlined in this protocol with reasonable safetySerious medical or psychiatric conditions that might limit the ability of the patient to comply with the protocolPregnant or lactating women

### Who will take informed consent? {26a}

One of the study investigators will obtain a written informed consent from every patient prior to the enrolment in the clinical trial. During the consent process, the risks and benefits of participating in the study will be discussed in the language (Hindi or English) that the patient comprehends. Consent will be entirely voluntary and free from any coercion.

### Additional consent provisions for collection and use of participant data and biological specimens {26b}

Apart from the intervention, participants will be asked to provide blood samples (5 ml) at two time points: one at baseline and the second at the end of four cycles of capecitabine, or at the development of HFS (whichever is earlier). This will be used to assess serum COX-2 levels by enzyme-linked immunosorbent assay (ELISA) at two time points and genetic polymorphism of DPD enzyme in the baseline sample.

### Interventions

#### Explanation for choice of comparator arm {6b}

Patients will be randomly allocated to one of the two arms: intervention (1% topical diclofenac) or control (placebo). Placebo was chosen as the comparator arm as there is no current standard of care intervention to prevent capecitabine-induced HFS. Further, the placebo will contain the base used for topical diclofenac gel, and this will ensure that the study will elucidate purely the effect of diclofenac.

#### Intervention description {11a}

This is a double-blind study. The intervention for this trial is 1% topical diclofenac gel, whilst the placebo contains the same base used for manufacturing diclofenac gel. The tubes will be manufactured and packed in a set of standard unlabelled tubes by Alkem Laboratories. These will be labelled by the statistician using the alpha-numeric codes generated for each randomization number. Other investigators and participants will be blinded.

The participant will be provided with a pack of 16 tubes (30 gm each) to suffice for topical application over 12 weeks. The participant will apply 1 g (1 g = two fingertip units [FTU]: one FTU for one surface of one hand) of 1% topical diclofenac or placebo on the palmar and dorsal surface of each hand twice daily until discontinuation of capecitabine or 12 weeks or development of HFS, whichever is earlier. The study drug will be stored in a locked compartment at room temperature.

#### Relevant concomitant care permitted or prohibited during the trial {11d}

All patients will be allowed to receive standard of care treatment as per the physician’s discretion. Supportive care drugs including but not limited to antiemetics, anti-diarrheal, antibiotics, and bone-modifying agents such as bisphosphonates will be permitted in the study. Oral non-steroidal anti-inflammatory drugs (NSAIDs) and aspirin will not be permitted in the study, and the patients who require these drugs will need to discontinue the study treatment after discussion with the principal investigator.

#### Criteria for discontinuing or modifying allocated interventions {11b} (drop out criteria)

Patients who meet any of the following criteria will discontinue the study treatment:Permanent discontinuation of capecitabine by treating physician (unacceptable toxicity or progression of underlying cancer).Completion of 12 weeks of the study period.The investigator determines that the continuation of treatment is not in the patient’s best interest.Occurrence of an exclusion criterion affecting patient safety, e.g. pregnancy or psychiatric illness.Required use of a concomitant treatment that is not permitted.Failure to comply with the protocol, e.g. repeatedly failing to attend scheduled assessments. If a patient has failed to attend scheduled assessments in the study, the investigator must determine the reasons and document the circumstances as completely and accurately as possible in the medical records.The patient declines further study treatment or withdraws their consent to participate in the study.

#### Strategies to improve adherence to interventions {11c}

Patients will be provided with a self-reported adherence diary at randomization to be filled daily (Fig. 1). This will be checked and adherence will be encouraged at each subsequent visit. Further, empty tubes will also be collected from the patient at each visit to check adherence.

**Fig. 1 Fig1:**
[figure not shown]
Self-reported adherence diary

#### Provisions for post-trial care {30}

Since there are no standard prophylactic interventions to prevent capecitabine-induced HFS, participants will follow the instructions provided by the treating oncologist. There is no provision to provide further topical medications after the end of the study period.

##### Ancillary and post-trial care

For prevention of hand-foot syndrome, no ancillary measures outside trial will be used. However, if the patients develop hand-foot syndrome, its treatment will be at the discretion of the treating oncologist. Likewise, post-trial care will be as per the treating oncologist.

### Outcomes {12}

The primary outcome of the study is the proportion of patients who develop grade 2 or higher HFS, as defined by the NCI CTCAE version 5.0 (Table 1).

**Table 1 Tab1:** NCI CTCAEv5.0 grading for HFS/palmar plantar erythrodysesthesia

Grade	Description
**Grade 0**	No symptoms
**Grade 1**	Minimal skin changes or dermatitis (e.g. erythema, oedema, or hyperkeratosis) without pain
**Grade 2**	Skin changes (e.g. peeling, blisters, bleeding, oedema, or hyperkeratosis) with pain; limiting instrumental ADL
**Grade 3**	Severe skin changes (e.g. peeling, blisters, bleeding, oedema, or hyperkeratosis) with pain; limiting self-care ADL

*ADL* activities of daily living

The primary, secondary and tertiary outcomes of the study are described in Table 2.

**Table 2 Tab2:** Primary, secondary and tertiary outcomes of the study

Outcome	Description
Primary outcomes	Grade 2 or higher HFS (proportion)
Secondary	All grades of HFS (proportion) Time to develop HFS (days) Patient-reported outcomes using HFS 14 questionnaire Adherence with topical application HFS related dose changes and delays in capecitabine Adverse events (NCI CTCAE version 5.0)
Tertiary	COX-2 levels

*HFS* hand-foot syndrome, *NCI* National Cancer Institute, *CTCAE* Common Terminology Criteria for Adverse Events, *COX-2* cycloxygenase-2

#### Participant timeline {13}

Patients will be followed up until the 21st day after the fourth cycle of capecitabine or development of grade 2 or higher HFS, whichever occurs first. Data collected for the study will include clinical characteristics and will be obtained from hospital records and routine laboratory investigations (Fig. 2). This includes baseline demographics, outcome measures, treatment details, and adverse events. Blood samples collected at the defined two time points will be labelled and stored at − 80 °C until the analysis is performed.

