#### Sample size {14}

We calculated the sample size for the study using the chi-square test. With 120 patients in each study arm, there will be at least 80% power to detect a difference in HFS rates at a two-sided 0.05 significance level, using a chi-square test. This assumes that the rate of grade 2 or higher HFS is 30% in the control arm and 15% in the experimental arm. Assuming approximately 10% attrition, we plan to recruit 264 patients.

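### Follow-up stops at the first grade 2 or higher HFS in one section and runs to the end of four cycles in another; the stop truncates dose-change, patient-reported and adverse event data, but not the primary outcome

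*Protocol article*

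**What the plan says.** Participant timeline {13} sets two end points for follow-up and takes the earlier: "Patients will be followed up until the 21st day after the fourth cycle of capecitabine or development of grade 2 or higher HFS". It counts outcome measures, treatment details and adverse events among the data collected. Abstract (Methods) gives only the first end point: "The patients will be followed up until the end of four cycles". The text provides for no data collection after a grade 2 or higher event. The data collection figure is not reproduced.

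Outcomes {12} makes the proportion with grade 2 or higher HFS the primary outcome. Its Table 2 lists as secondary, among others, PROs, adverse events and "HFS related dose changes and delays in capecitabine". Objectives {7} measures dose changes as the number of patients with an HFS-related modification, and brings in HFS severity only through the tertiary correlations with COX-2 and DPD. Background {6a} explains why dose changes follow HFS: "In severe cases, however, it may necessitate dose interruptions, modifications, and permanent discontinuation of capecitabine".

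Visits are every 3 weeks (section {18b}). Section {20c} includes all randomized patients by intention-to-treat and checks missing data with Little's test.

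**The concern.** Ending follow-up at the event suits an outcome that only asks whether, or when, the event first happens. It does not suit outcomes that are consequences of the event or that accrue after it. Here the censoring event is the one the gel is meant to prevent, so if the gel works, the amount of censoring differs by arm.

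The direction of bias varies by outcome. Losing later dose changes and poor PRO scores mainly on placebo tends to hide a benefit. Longer observation on diclofenac tends to raise its adverse event count. The planned analysis cannot repair this. Intention-to-treat keeps patients in their randomized arm but does not supply data that were never collected. Little's test cannot help where the loss depends on the outcome by rule.

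**Working it through.** **Inputs.** From Sample size {14}: "the rate of grade 2 or higher HFS is 30% in the control arm and 15% in the experimental arm"; "With 120 patients in each study arm, there will be at least 80% power"; 264 recruited, so 132 per arm at 1:1. From Objectives {7}: a 12-week assessment period. From Background {6a}: HFS peaks in cycle 2. The documents give no mean event time, so I assume week 6, with a range of week 3 to week 9.

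**Plan's own figure.** The pooled-variance formula for 30% vs 15%, two-sided 0.05 and 80% power gives 121 per arm. With 120 per arm, power is 79.8% by the normal approximation and 80.5% by exact enumeration of the uncorrected chi-square test. 240 × 1.10 = 264. The stated size is reproduced within rounding.

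**Patients truncated (arm size × event rate).**
- Of 132: placebo 132 × 0.30 = 39.6; diclofenac 132 × 0.15 = 19.8; together 59.4.
- Of 120: 36 and 18.
- The 2:1 ratio is simply 0.30/0.15. With no treatment effect it is 1:1.

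**Person-time observed, 1 − rate × (12 − t)/12.**

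| Mean event time t | Placebo | Diclofenac | Ratio |
|---|---|---|---|
| Week 3 | 1 − 0.30 × 0.75 = 77.5% | 1 − 0.15 × 0.75 = 88.75% | 1.15 |
| Week 6 | 1 − 0.30 × 0.50 = 85.0% | 1 − 0.15 × 0.50 = 92.5% | 1.09 |
| Week 9 | 1 − 0.30 × 0.25 = 92.5% | 1 − 0.15 × 0.25 = 96.25% | 1.04 |

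At week 6 the follow-up lost per randomized patient is 0.30 × 6 = 1.8 weeks on placebo and 0.15 × 6 = 0.9 weeks on diclofenac.

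**Adverse event illustration.** Take a true 12-week risk of 20% in both arms, constant hazard, independent of HFS. The risk by week 6 is 1 − 0.80^0.5 = 10.6%.
- Placebo: 0.70 × 20% + 0.30 × 10.6% = 17.2%.
- Diclofenac: 0.85 × 20% + 0.15 × 10.6% = 18.6%.
- False excess on diclofenac: 1.4 points (2.2 for a cut at week 3, 0.7 at week 9).

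**PROs.** Suppose grade 2 or higher HFS worsens the end-of-treatment score by D. The arm difference through that route is (0.30 − 0.15) × D = 0.15 × D. Among patients still followed at that point nobody has had the event, so the difference through that route is 0.

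**Dose changes.** A modification decided at the event visit is recorded. If a fraction f of event patients have their first HFS-related modification later, the patients missed are 39.6 × f on placebo and 19.8 × f on diclofenac, and the arm difference is understated by 0.15 × f. The documents give no value for f.

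**Later worsening to grade 3.** If 10% to 50% of event patients worsen from grade 2 to 3 after first detection (assumption), about 4 to 20 such cases go unrecorded on placebo and 2 to 10 on diclofenac. A case first seen at grade 3 is still recorded.

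**The case against.** The strongest reply is that little of importance is lost. Much of it stands.

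- **Main endpoints.** A reader might infer that the primary result is biased. It is not: the first grade 2 or higher event is counted before follow-up stops, and by then any-grade HFS and its onset have also occurred.
- **Grade 3.** It is tempting to call grade 3 progression a lost secondary outcome. Neither Objectives {7} nor Table 2 lists it; later worsening bears only on the tertiary severity correlates.
- **Twice as often on placebo.** This is the design alternative, not a fact. Under no effect the loss is equal in both arms, though still tied to the outcome.
- **A PRO difference of zero.** This needs an end-of-treatment comparison among those still followed, with HFS as the only route of effect. The text fixes no PRO time point, and an event-visit, worst or last value would keep some of the signal.
- **Dose changes.** One record per patient suffices for the measure in Objectives {7}, and hospital records are a data source. The loss is real for first changes made later, but its size is unknown. Table 2 also lists delays, and later ones are lost as well.
- **Safety on gel only.** Intervention description {11a} ends the gel at HFS, so much of the lost time is off-gel, and on-gel safety is a defensible target. But that section gives no HFS grade, whereas follow-up stops at grade 2, so the follow-up rule does not define an on-gel window.

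The missing figure might show later visits, and the abstract might be the true intent. Either would leave the sentence in the participant timeline needing correction.

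**Conclusion.** The concern holds for secondary outcomes and should be fixed; it does not threaten the trial's main conclusion. Two statements of the follow-up period conflict. The more specific one stops data collection at the primary event, which truncates later dose changes and delays, later PROs and later adverse events.

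The counts of about 40 and 20 of 132 rest on the planned 30% and 15%. The adverse event distortion is modest and rests on the assumed event time. The PRO loss is conditional on how and when PROs are compared, and the dose-change loss cannot be sized from the documents. Those last two carry most of the weight, because they are the outcomes through which preventing HFS would be expected to show its value.

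**What to change.** In Participant timeline {13}, delete the clause that ends follow-up at "development of grade 2 or higher HFS, whichever occurs first", so that it agrees with the abstract. Collect HFS grade, capecitabine changes, PROs and adverse events on every patient to the 21st day after cycle 4, or to the same calendar point if capecitabine stops early. Use the existing 3-weekly visits, telephone contact or hospital records.

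Keep the follow-up rule separate from any rule on stopping the gel. The gel-stopping text in Intervention description {11a} names HFS without a grade, and section {11b} does not list HFS, so those two also need reconciling.

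For patients whose follow-up has already ended at HFS, retrieve dose changes and adverse events from hospital records where possible; their later PROs cannot be recovered.

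**Cost.** This is a mid-trial amendment (75 patients were recruited by 25 August 2021), to be reported to the ethics committee and the registry. Extra data collection falls on about 60 patients at the design rates, some of whom may no longer attend for capecitabine. Truncation by the outcome falls from an expected 30% vs 15% to none by rule. N = 264 and the primary analysis are unchanged.
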